## Results

Data will be imported from Excel 2019 to IBM SPSS version 26.0 for inferential statistical analysis. The normal distribution of the data will be checked before determining the descriptive statistics for all variables (means and standard deviations). The participants’ basic information will be descriptive, including age, gender, and BMI. The primary outcomes will be expressed as continuous. If data are approximately normal distribution, the effect of the PE curriculum intervention on dependent variable (FMS, or TGMD, or HTKS, or SCEB score) will be investigated with repeated ANOVAs within factor: time (pre and post), between factors: group (HS, OPE, and FP) and gender (boy and female) and Bonferroni post hoc tests. Further, the relationship between FMS and other domains will be identified by regression analysis. Finally, the potential influence of individual factors (such as age, gender, and temperament) on the intervention effect will be investigated by comparing the gain in FMS score and subscale. Multiple regression equation is used to further explore the extent to which social-ecological factors contribute to the FMS score level at baseline. Statistical significance will be set at *P* < 0.05.

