## Materials and methods

The study protocol complies with the guidelines of the SPIRIT 2013 statement (Chan *et al.*, 2013). The trial was registered with the Chinese Clinical Trial Registry (registration number: ChiCTR2000035414) on 10 August 2020 and will be carried out in accordance with the Declaration of Helsinki.

Children, aged 4–6 years, from three predetermined kindergartens will participate. The three kindergartens are categorized based on three different PE programs provided for the children: a Hello Sunshine (HS), an ordinary PE (OPE), and a free play (FP) depending on their existing PE curriculum.

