## Sample size determination

We used WinPepi software to calculate the sample size with reference to Westendop’s research (2014) while ensuring it would be larger than those used in other comparative studies (Robinson *et al.*, 2017; Taunton, Mulvey and Brian, 2018). The following assumptions were used: significance level of 5%; power of 80%; and confidence level of 95%, inflated to compensate for a 5% non-inclusion rate. As a result, at least 249 children (83 in the HS group, 83 in the OPE group, and 83 in the FP group) will participate in this study.

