## Randomization

The children aged 4–6 years within four classes (two classes selected from K2 and K3 grade, separately) will be randomized from the designated kindergartens using Research Randomizer software. The preschoolers in each class who meet the eligibility criteria will be screened by the kindergarten teachers and staff. To avoid changes in teachers and classmates affecting the results of this course, we will intervene in the form of a nature class. In total, 12 nature classes in grades K2 and K3 from the 3 kindergartens will be assigned to a PE curriculum in their respective schools, that is, 4 classes in the sport-featured kindergarten with “Hello sunshine” PE curriculum, the OPE group will have ordinary PE classes, the PE class in the FP group will be free play. This sequence will then be concealed in an opaque envelope.

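### Whole classes receive the curriculum, but the stated outcome model has no class term, so its standard errors are too small if gains correlate within class

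*Protocol article*

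**What the plan says.** The *Randomization* section makes the class the unit of delivery: "we will intervene in the form of a nature class". It then fixes the number of classes: "In total, 12 nature classes in grades K2 and K3 from the 3 kindergartens will be assigned to a PE curriculum in their respective schools". Each arm therefore has four classes and one kindergarten. *Materials and methods* confirms that arm and kindergarten coincide: "The three kindergartens are categorized based on three different PE programs provided for the children".

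The *Results* section states the effect analysis as "repeated ANOVAs within factor: time (pre and post), between factors: group (HS, OPE, and FP) and gender (boy and female", followed by Bonferroni post hoc tests at P < 0.05. The dependent variables it lists are FMS or TGMD, HTKS and SCEB scores. It mentions no class or kindergarten effect, mixed model, cluster-robust error or class-level analysis.

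*Sample size determination* gives "at least 249 children (83 in the HS group, 83 in the OPE group, and 83 in the FP group". Its listed inputs, "significance level of 5%; power of 80" per cent and a sample "inflated to compensate for a 5% non-inclusion rate", include no ICC or design effect.

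**The concern.** Children in one class share a teacher, lessons, outdoor supervision and classmates. The article keeps classes intact precisely so that changes in these do not disturb the results, which accepts that class membership matters. If a class does unusually well or badly over the 10 weeks, all its children move together, and about 21 correlated gains carry less information than 21 independent ones. The planned ANOVA counts them as independent, with 249 − 6 = 243 error degrees of freedom once group, gender and their interaction are fitted. Only 12 − 3 = 9 degrees of freedom exist between classes within arms.

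For SCEB-30 the dependence comes from the measurement itself. *Study procedure* has the head teacher of each class complete the scale, so a drift in that teacher's standard between pre and post shifts every child in the class.

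At stake is the main claim, that HS improves these outcomes more than OPE or FP. Ordinary class-to-class variation in gain could be read as a curriculum effect, in a project whose results are meant to inform policy.

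**Working it through.** **Inputs from the article.** 249 children, 83 per arm; 12 classes (*Abstract* and *Randomization*; *Participants* speaks of two classes in K2-K3, and the figure of 12 is used here); alpha 5%; power 80%. Mean class size m = 249/12 = 20.75.

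**Input assumed.** The class ICC of the pre-post gain, ρ, from 0.01 to 0.20. The ICC of the gain is the one that matters, because stable differences between classes cancel in a group-by-time test.

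**The stated sample size.** No effect size or SD is given, so 83 can only be back-solved. With a two-sided test and an assumed standardised difference of 0.45, n = 2(1.960 + 0.842)²/0.45² = 77.5, rounded up to 78, and 78/0.95 = 82.1, rounded up to 83. Individual-level inputs alone therefore can reproduce 83, with no allowance for classes. This shows consistency only; it does not prove how 83 was obtained.

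**Effect on the planned test.** With two time points, the group-by-time F test is the F test of group on the gain.

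- Design effect: DE = 1 + (m − 1)ρ = 1 + 19.75ρ.
- Standard errors are too small by the factor √DE.
- Effective children per arm: 83/DE.
- Hand approximation for the three-group test: type I error ≈ 0.05^(1/DE), because with large error df the F statistic on 2 df has tail probability exp(−f).
- Simulation: 10,000 trials per ICC with no true effect, 12 classes of 20 or 21, gain analysed on group, gender and their interaction.

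| Assumed ρ | DE | √DE | Effective n per arm | Type I error, hand | Type I error, simulated |
|---|---|---|---|---|---|
| 0 | 1.00 | 1.00 | 83 | 5.0% | 5.0% |
| 0.01 | 1.20 | 1.09 | 69 | 8.2% | 8.6% |
| 0.02 | 1.40 | 1.18 | 60 | 11.7% | 12.1% |
| 0.05 | 1.99 | 1.41 | 42 | 22.2% | 21.5% |
| 0.10 | 2.98 | 1.72 | 28 | 36.5% | 36.4% |
| 0.20 | 4.95 | 2.22 | 17 | 54.6% | 55.8% |

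Further simulations differ from these by no more than about 1.5 percentage points.

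**Bonferroni does not repair this.** In the same runs, at least one Bonferroni-adjusted pair was significant in 7.7%, 11%, 20%, 34% and 54% of null trials for ρ = 0.01 to 0.20. The adjustment corrects for three comparisons, not for a wrong standard error.

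**Class-level analysis.** An F test on the 12 class means (2 and 9 df) rejected in 4.9% to 5.2% of null trials across the whole range of ρ, provided there was no kindergarten effect.

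**What the class level cannot repair.** Let k and c be the kindergarten and class shares of the variance of the gain. An arm mean then has variance k + c/4 + (1 − k − c)/83, but the class-mean test estimates only the last two terms.

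- c = 0.05, k = 0.01: 0.0338 against 0.0238, ratio 1.42. Type I error is P(F(2,9) > 4.256/1.42) = 10%.
- c = 0.05, k = 0.05: 0.0733 against 0.0233, ratio 3.14. Type I error is 31%.

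Simulation gave 9.5% and 31%. Both k values are assumptions. With one kindergarten per arm, the trial cannot estimate k.

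**The case against.** The best defence is that a journal article condenses the plan and a fuller analysis plan may handle clustering. That would answer an omission, but here a specific model is written down, and it conflicts with the stated delivery unit. A later plan would have to replace it.

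Four stronger readings might be inferred, and the article does not support them:

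- **That false-positive rates far exceed 5% in any case.** No ICC is given. At 0.01 the excess is modest (about 8%); it becomes large from roughly 0.02 upward.
- **That every primary outcome is affected.** *Results* names FMS/TGMD, HTKS and SCEB for this model. Table 1 also lists anthropometrics and physical fitness as primary, and the article does not say by name that they get the same ANOVA.
- **That the post hoc tests compare group means averaged over pre and post, and so dilute a real effect.** An ANOVA with time within and group between contains group-by-time, and *Hypotheses* targets greater improvement in HS. Nothing says that the post hoc tests will use time-averaged means, and that level of detail may be left to a fuller plan.
- **That a class-level model makes the comparison valid for the curriculum.** It does not, because each arm is a single kindergarten. *Strengths and limitations* calls for randomised trials in more kindergartens but does not state this consequence.

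**Conclusion.** The point holds, with its size conditional on the ICC. The article delivers the intervention to intact classes and fixes an analysis that ignores them, so the error terms for FMS/TGMD, HTKS and SCEB are too small whenever gains are positively correlated within class. Over an assumed gain ICC of 0.01 to 0.20, the type I error runs from about 8% to 56%, and is about 22% at 0.05. These figures assume 12 classes of about 21 and no kindergarten effect on change. SCEB-30 is the most exposed outcome because rater and class coincide.

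Correcting for class is necessary but not sufficient: a class-level P value speaks to the curriculum only if the three kindergartens would otherwise have changed alike. This needs fixing before analysis, because the main between-arm claims rest on this test.

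**What to change.** Replace the repeated-measures ANOVA with a linear mixed model, which the planned SPSS software can fit with MIXED:

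- group-by-time as the tested effect, with the HS-OPE and HS-FP contrasts on change reported with confidence intervals;
- fixed effects for grade (K2/K3) by time and for gender. Grade is needed because classes come from two grades and the HS schedule differs between them;
- a random child effect, or an unstructured pre/post covariance within child. Without it, a child's two scores are treated as independent given class. In simulation with an assumed within-child correlation of 0.6, null rejection then fell below 0.5% for a gain ICC of 0 to 0.02 and to about 2% at 0.05, which wastes power;
- random class and random class-by-time. A class intercept alone cancels out of change and corrects nothing;
- Satterthwaite degrees of freedom.

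As a check, analyse the 12 class-mean gains by group with a grade term: 12 − 3 − 1 = 8 error df.

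Add to the limitations that each arm is one kindergarten, that no analysis can separate curriculum from kindergarten, and that the class-level P values apply to the curriculum only if there is no kindergarten-level effect on change. Word the conclusions to match.

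The cost is wider intervals and lower power. For a single pairwise contrast with 8 df and an assumed difference of 0.446 SD of the gain (close to the back-solved value), power is about 71% at ICC 0, 63% at 0.01 and 43% at 0.05, against the planned 80%. No new data are needed. The kindergarten limit would remain unless more kindergartens were added to each arm.

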### Covariate and mediator

#### Personal factors

Age will be calculated as the children’s month-based ages, as it is going to affect the intervention’s outcome. Participants’ perceived motor competence will be measured with a pictorial scale for perceived movement skill competence (PMSC) that builds upon the TGMD-2 (Barnett *et al.*, 2015). It consists of 13 pictures illustrating cartoon boys (boy version) or girls (girl version) performing TGMD-3 skills. It shows middle to high instrument reliability and face validity in Chinese children (Diao *et al.*, 2018). Children will be shown illustrations by the examiner and judge whether the cartoon character is good at doing the skills, then choose between four Likert scale options (1 to 4, from “not too good” to “really good”).

Individual temperaments are expected to be predictive of the differential effects of this motor skills intervention (Taunton *et al.*, 2018), and they will be assessed using the 36-item Children’s Behavioral Questionnaire-Very Short Form (CBQ-VSF) (Putnam and Rothbart 2006). The test is divided into three broad dimensions: surgency, negative affect, and effortful control and it demonstrates acceptable internal consistency. It is a very short form based on the well-established parent report measure of temperament CBQ questionnaire for children aged 3 to 8 years (Rothbart *et al.*, 2001) and it has medium to high reliability and validity confirmed by studies in multiple countries. The CBQ-VSF provides moderate reliability of scale scores for assessing temperamental characteristics in preschoolers (de la Osa *et al.*, 2014).

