### Strengths and limitations

One of the strengths of this project is that the quasi-experimental study comparing three parallel groups of PE in kindergartens using blinded assessors. This study design is implemented in realistic environment where the kindergartens are likely to be more cooperative as they can keep their existing curriculum arrangements. The HS group is mainly focused on ball skills, the other two teaching methods represent the mainstream PE activities employed in most kindergartens; the OPE group covers multiple types of physical activity taught by PE teachers, and the control group’s main characteristic is FP. Our research will involve a comprehensive quantitative analysis of the immediate and follow-up effects of the interventions on four domains of children’s development and will collect information from multiple informants including from children, their parents, and their teachers. Finally, the impact of social-ecological factors on the interventions’ effects will be analyzed.

A limitation of this research will be the large number of items tested in this project, as these will take more time to collect and may stress the children’s patience levels. The short forms of each of the established tests have been selected. Exercise interventions in outdoor environments are also affected by weather conditions, including rain, and/or overheating during high temperatures, and the effects of the COVID-19 pandemic. Such factors may affect both delivery and compliance. Further randomized controlled trial studies conducted in more kindergartens will broaden our understanding of the impact of ball skills learning on children’s development, and a cohort study will be established to explore the long-term effects of ball skill learning on children.

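### The HS/OPE/FP comparison of pre-post change leaves out age in months, a covariate the protocol itself says will affect the outcome

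*Protocol article*

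**What the plan says.** **Group model.** The Results section names the model for the intervention effect: "repeated ANOVAs within factor: time (pre and post), between factors: group (HS, OPE, and FP) and gender (boy and female", followed by Bonferroni post hoc tests. No covariate is listed.

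**Age.** Under Covariate and mediator, Personal factors, age in months is the first item. It is to be calculated "as it is going to affect the intervention" outcome. The Results section uses age in two other ways: as a descriptive characteristic, and in a later comparison of FMS gains across individual factors. The multiple regression described there explains the FMS level at baseline, not the group effect.

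**Arms.** Materials and methods assigns the three kindergartens to programmes "depending on their existing PE curriculum". Strengths and limitations counts it as an advantage that "they can keep their existing curriculum arrangements". Under Participants, HS is a sport-featured kindergarten, OPE a public one and FP an inclusive private one. Under Randomization, four classes are drawn in each, two from K2 and two from K3.

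**The concern.** Random selection of classes within a kindergarten does not make the three kindergartens comparable. Age is an obvious way in which they may differ: all outcomes are developmental, the eligible range is 4 to 6 years, and the protocol expects age to matter. The only between-child factor in the group model besides group is gender.

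An effect of age on the level of a score does no harm here, because it is the same before and after and cancels in the change. The harm comes if older and younger children gain at different rates over the 10 weeks. Part of any age difference between kindergartens would then be read as a curriculum effect, or would mask one. The contrast affected is the central one: the Hypotheses section predicts significantly greater improvement in HS than in OPE and FP.

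**Working it through.** **1. What the planned test compares.** With two time points, the group-by-time F of a repeated-measures ANOVA equals the one-way ANOVA F on post minus pre. On a simulated three-group data set with 83 per group, both routes gave F = 0.2111. The planned contrast is therefore a difference in mean raw change.

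**2. The plan's own size figure.** Sample size determination gives "at least 249 children (83 in the HS group, 83 in the OPE group, and 83 in the FP group", with "significance level of 5%; power of 80%; and confidence level of 95%, inflated to compensate for a 5% non-inclusion rate". No effect size or SD is printed, so 83 can only be back-solved:
- Two-sided, assumed d = 0.45: n = 2 × (1.960 + 0.842)² / 0.45² = 77.5, so 78; 78 / 0.95 = 82.1, so 83.
- One-sided, assumed d = 0.40: n = 2 × (1.645 + 0.842)² / 0.40² = 77.3, so 78, and again 83.

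The point does not depend on this figure; it only gives a scale.

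**3. Bias from leaving out age.** Let G be the difference in mean age between two kindergartens, in SDs of age. Let k be the extra gain, in SDs of the outcome, per SD of age. With no true effect, the expected difference in change is G × k. Neither value is in the documents, so the following are assumptions:

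| Age gap G | Extra gain k | Bias G × k |
|---|---|---|
| 0.25 | 0.1 | 0.025 SD |
| 0.25 | 0.2 | 0.05 SD |
| 0.5 | 0.1 | 0.05 SD |
| 0.5 | 0.2 | 0.10 SD |

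To give G a meaning: if ages were spread evenly over the 24 months from age 4 to age 6, the SD would be 24/√12 = 6.9 months, and a 0.5 SD gap would be about 3.5 months. With equal sampling by grade, that is a large gap.

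**4. Effect on the error rate, bottom row of the table.** Take 83 per group, a baseline SD of 1 and a pre-post correlation of 0.7 before the age term.
- Variance of change = 2 × (1 − 0.7) + 0.2² = 0.64.
- Standard error of the difference = √(0.64 × 2/83) = 0.124.
- Shift = 0.10 / 0.124 = 0.81 standard errors.
- False-positive rate: about 13% at an uncorrected two-sided 5%. The simulation (2,000 runs, two groups) gave 13%.
- At 0.05/3, as Bonferroni for three pairwise contrasts implies: about 6% per contrast, against a nominal 1.7%.

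In the same simulation, a model of the post score on group, baseline score and age gave an estimate near 0 and a rejection rate of about 5%.

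**5. Change versus baseline adjustment.** In simulations with 83 per group, no true effect, a 0.5 SD baseline gap and a slope or reliability of 0.7:

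| True situation (assumed) | Change analysis | Baseline-adjusted |
|---|---|---|
| Post score depends on observed baseline | bias 0.15 SD, rejects about 23% | bias about 0, rejects 4–5% |
| Stable gap, parallel growth | bias about 0, rejects about 5% | bias 0.15 SD, rejects about 25% |

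Each method fails where the other succeeds, and the documents do not say which situation applies.

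**The case against.** The strongest reply is that the planned analysis is a recognised estimator and that the design already limits age imbalance. Much of this stands.

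- **Age is partly handled.** Equal sampling from K2 and K3 gives rough balance, and the Results section looks at age against FMS gain. The heading Covariate and mediator does not promise that age will adjust the group contrast, so this is not a strict contradiction. But grade balance is not balance in months. The gain comparison covers FMS only and does not adjust the HS/OPE/FP contrast. The text gives no reason for leaving out a variable it calls influential.
- **A reader might infer that the analysis ignores the baseline score.** It does not: the pre score is the first level of the time factor, so a stable gap between kindergartens cancels.
- **A reader might also infer that the change analysis is wrong and baseline adjustment right.** Step 5 does not support that. Intact kindergartens with long-standing curricula could well show stable gaps, the case in which change is unbiased. Children were not assigned by test score, so regression to the mean alone does not favour adjustment. Ceiling effects on bounded scales such as HTKS (0 to 52) are possible, but no score distribution is given.
- **Uncorrected two-group error rates overstate the planned test.** With Bonferroni post hoc tests, the age example falls from about 13% to about 6% per contrast.

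A sensitivity model might properly be left to an analysis plan that is not shown. The named main model and its factors are fixed in the article, so the omission of age is open to comment.

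**Conclusion.** The point holds for age. The protocol fixes a comparison of raw change between three non-randomised kindergartens and omits a covariate it expects to influence the outcome. The contrast is biased only if two things are both true: mean age differs between kindergartens despite grade sampling, and gains depend on age. Under the assumed ranges the bias is 0.025 to 0.10 SD. The upper value is about one fifth of the back-solved 0.45 SD (0.10 / 0.45 = 0.22), if both are in the same SD units. None of these inputs is printed, so the true size is unknown and could be negligible.

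The documents do not support the stronger conclusion that the choice of change scores is itself an error, or that an HS effect should be claimed only if a baseline-adjusted model agrees. The latter is a debatable trade-off that costs power.

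**What to change.** In the Results section, add age in months as a covariate, together with its interaction with time, to the repeated-measures model for each outcome. The interaction is the part that matters, since an age effect on level alone already cancels.

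As a labelled sensitivity analysis, also report a model of the post score on group, gender, age in months and baseline score. State that in non-equivalent groups the change and baseline-adjusted estimates rest on different assumptions and that neither is automatically unbiased. Where the two lead to different conclusions, report the result as dependent on the assumption.

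The cost is one covariate and one extra model per outcome, on data already collected, and a few lines of text. The article should also say what adjustment cannot do: with one kindergarten per arm, it cannot separate the curriculum from other differences between the kindergartens.

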### Study procedure

After conducting the preliminary research work, the researchers will contact three kinds of kindergartens in this district and communicate with the directors to enquire whether they are interested in research on the health benefits of physical activity in young children. It was agreed that once the study has been approved by the ethics committee, the researchers will recruit participants from selected kindergartens. The kindergartens will send invitations to parents, along with information about the project and an informed consent form. After the collection of the signed consent forms, eligible participants will be screened by the kindergarten teachers, and the researchers. The baseline measurements will be conducted in the initial 2 weeks and all the participants will experience the same assessment at the end of the 10 weeks intervention. The experimental process will be administered as shown in the flow diagram (Figure 2). The physical fitness test, TGMD-3 test, and psychological test (PMCS and HTKS) tasks will be tested in random order in each kindergarten and based on their schedules and space availabilities both at baseline and after 10 weeks intervention, should finish within 4 days in each kindergarten with trained research students responsible for grouping the test items. All children will be encouraged with snacks or stickers to complete all tests. Video recordings will be used for later scoring and checking. The participants will be given a separate and quiet space to take the psychological test. Parents will receive their digital-based questionnaires at a parents’ meeting. They will fill these out and submit them on the day. The head teacher of each class will fill in the SCEB-30 questionnaire in 1 week.

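### The curriculum effect is tested by a child-level repeated ANOVA with no class term, although whole classes are taught together; if gains correlate within class, the nominal 5% error rate is not held

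*Protocol article*

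**What the plan says.** The Results section of the protocol article fixes the effect test for the FMS, HTKS and SCEB scores as "repeated ANOVAs within factor: time (pre and post), between factors: group (HS, OPE, and FP) and gender (boy and female", followed by Bonferroni post hoc tests. It adds: "Statistical significance will be set at *P* < 0.05". The factors are listed by name. Class, grade and kindergarten are not among them, and no mixed model or cluster-robust error is mentioned.

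The Randomization section describes a different unit of delivery: "we will intervene in the form of a nature class", and the total is "12 nature classes in grades K2 and K3 from the 3 kindergartens", each class following the curriculum of its own school. Under Study procedure, "The head teacher of each class will fill in the SCEB-30 questionnaire in 1 week". Table 1 lists that scale as a primary outcome.

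The Sample size section lists "significance level of 5%; power of 80%; and confidence level of 95%, inflated to compensate for a 5% non-inclusion rate" and arrives at "at least 249 children (83 in the HS group, 83 in the OPE group, and 83 in the FP group". No ICC or design effect is among the stated assumptions.

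**The concern.** With two time points, the group-by-time test is the same as an ANOVA of each child's gain on group (and gender). The planned error term is the spread of gains between children, as if all 249 were independent. Children in one class share a class teacher, classmates and, in the HS and OPE arms, PE lessons. The Randomization section keeps classes intact precisely because changes of teachers and classmates could affect the results. For the SCEB-30 they also share a single rater, so any drift in that teacher's standard between the two occasions moves the whole class.

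If gains therefore vary from class to class, the planned test counts that variation as evidence for a curriculum. This test answers the main hypothesis, and the Conclusions section states a policy-advocating aim. The model is written out in the protocol with its factors named, so the omission is a stated choice and not a detail left to an analysis plan.

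**Working it through.** **Inputs from the protocol.** 249 children, 83 per arm; 12 classes, four per arm (Abstract, Randomization); nominal level 0.05; three groups, so three pairwise comparisons and a Bonferroni level of 0.05/3 = 1.67%.

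**Assumed input.** The ICC of gains within class, which the protocol does not give: range 0.01 to 0.20. It is the ICC of the change score that matters, because class differences that are stable over time cancel in group-by-time.

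**The plan's own figure.** 249 cannot be reproduced, because no effect size or SD is stated; the section says only "We used WinPepi software to calculate the sample size with reference to" an earlier study. Solving backwards for a two-sided 5% two-group comparison with 80% power: 78 per arm gives 78/0.95 = 82.1, rounded up to 83, and implies d = (1.960 + 0.842) × √(2/78) = 0.449. This d is inferred, not stated.

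**Degrees of freedom.** The planned test has 249 − 6 = 243 error df (three groups by two genders). Between-class variation has 12 − 3 = 9 df, or 8 once a grade term is added.

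**Design effect.** Mean class size m = 249/12 = 20.75, and DE = 1 + (m − 1) × ICC = 1 + 19.75 × ICC. A single contrast tested at critical value c has true error of about 2 × [1 − Φ(c/√DE)], with c = 2.394 at the 1.67% level. For ICC 0.05: DE = 1.99, 2.394/1.41 = 1.70, error about 9%.

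**Simulation with no true effect.** 40,000 trials per ICC, 12 classes of 20–21 children, no kindergarten effect, gender left out:

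| ICC of gains (assumed) | DE | Effective n of 249 | Group-by-time F, nominal 5% | One contrast, nominal 1.67% | 12 class means, 9 df |
|---|---|---|---|---|---|
| 0 | 1.00 | 249 | 4.9% | 1.6% | 4.7% |
| 0.01 | 1.20 | 208 | 8.0% | 2.8% | 5.0% |
| 0.02 | 1.40 | 179 | 11.8% | 4.4% | 5.1% |
| 0.05 | 1.99 | 125 | 22.2% | 8.9% | 4.9% |
| 0.10 | 2.98 | 84 | 37.0% | 16.8% | 5.0% |
| 0.20 | 4.95 | 50 | 56.0% | 29.4% | 5.0% |

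Other runs agree to within about one percentage point (for example 57% in place of 56% at ICC 0.20).

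**Do gender and Bonferroni help?** With gender and its interaction with group included (8,000 runs per ICC), the F test errs in 8.4%, 11.8%, 22.1%, 36.4% and 55.9% of trials at ICC 0.01 to 0.20. At least one false Bonferroni result occurs in 7.7%, 10.8%, 20.7%, 34.5% and 54.2%. Neither step repairs the test.

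**Grade.** Each arm has two K2 and two K3 classes, and the HS schedule differs by grade. If gains differ by an assumed 0.3 SD between grades, the 9-df class-mean test becomes conservative, with an error of about 1–4%. Adding grade (8 df) restores about 5%.

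**Power.** At the back-solved d = 0.449 with 78 per arm, a class-level pairwise t test on 9 df has power of 70%, 63%, 57%, 44% and 32% at ICC 0, 0.01, 0.02, 0.05 and 0.10.

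**The case against.** The strongest objection is that the inflation is conditional. The protocol reports no ICC, stable class differences cancel in the change score, and the 37–57% figures rest on assumed ICCs of 0.10–0.20. This stands: the direction follows for any positive ICC of gains, but the size is not established by the document.

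Part of the exposure is also not organised by class. FP children play without teacher guidance, HS children choose their own ball club, and no section says that PE teachers differ between classes of one kindergarten. This may lower the class-level ICC, but it gives no reason to set it to zero, and the single-rater argument for the SCEB-30 is untouched. That argument covers one outcome only.

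A reader might also infer that children of a class are tested together. The Study procedure section does not say so: tests run in random order within each kindergarten over 4 days. That source of correlation should not be claimed.

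Finally, one might say that the point is moot because each arm is one kindergarten. The two problems are separate. The class problem can be repaired with the data collected; the kindergarten problem cannot.

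**Conclusion.** The analysis as written is wrong for the design: it omits the unit in which the curriculum is delivered and, for the SCEB-30, rated. If gains correlate at all within class, the P values are too small. The group-by-time test then errs in about 8% of trials at an ICC of 0.01, about 22% at 0.05 and 56–57% at 0.20, against a nominal 5%. Confidence is high on the direction; the size depends on an ICC that the protocol does not supply.

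Two stronger readings are not supported. The first is that the error rate is known to be badly inflated: that would need a documented ICC. The second is that a class term makes the comparison between curricula valid. It holds the error rate only if there is no kindergarten effect. Adding a kindergarten variance of 0.02 or 0.05 (as a share of total variance) to a class ICC of 0.05 raises the error of the class-level test to about 15% or 31%. The class term is necessary but not sufficient.

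**What to change.** - In the Results section, replace the repeated ANOVA with a linear mixed model (SPSS MIXED, in the package already named). Keep group, time and gender, add grade (K2/K3) and grade by time, and include a random class effect on change (class by time).
- Test group contrasts on small-sample df, about 8 with grade in the model, and keep the Bonferroni adjustment.
- As a check, report an ANOVA of the 12 class mean gains on group and grade.
- State that this protects against class-level variation only, and that kindergarten-level differences remain inseparable from the curriculum effect.
- In the Sample size section, drop the 80% power claim or restate it with an allowance for class clustering.
- Reconcile the Participants section, which speaks of two classes in K2–K3, with the Randomization section, which speaks of four, because the number of classes sets the df.

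No new data are needed. The cost is wider confidence intervals and lower stated power than now claimed.
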